### Participants

Patients aged over 18 years who are classified as American Society of Anesthesiologists (ASA) physical status I–II, diagnosed as having lumbar spinal stenosis/intervertebral disc herniation/spondylolisthesis, requiring lumbar spinal decompression and 3–5 levels of bone graft fusion surgeries will be enrolled in the study after signing a written informed consent.

Patients with past medical history of chronic renal dysfunction (preoperative blood creatinine > 120 mmol/L), liver dysfunction (preoperative blood aspartate aminotransferase (AST) or alanine aminotransferase (ALT) > 50 U/L), coronary artery disease with stent placement, abnormal preoperative coagulation profile (preoperative prothrombin time (PT) elongation > 3 s, activated partial thromboplastin time (APTT) elongation >10 s, platelet counts < 100 × 10^9^/L or > 400 × 10^9^/L, or international normalized ratio (INR) > 1.4), or pre-existing anemia (male < 12 g/dL, female < 11 g/dL), and those who have long-term medications of aspirin and/or other anticoagulants, known allergy to TXA, or religious and/or other beliefs limiting blood transfusion are excluded. Participants who undergo dura mater laceration or unexpected massive bleeding or who receive cell saver application during operation will also be excluded.

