### Intervention

On the morning of the surgery, the appointed nurse will prepare Solutions A, B, and C according to the treatment allocation and the patient body weight (Wt, in kilograms) checked with ID number, with 100 ml Solution A as the loading dose, 100 ml Solution B as the maintenance dose, and 250 ml Solution C as the bolus dose. In the tTXA group, Solution A consists of 100 ml 0.9% normal saline (NS), Solution B consists of 100 ml 0.9% NS, and Solution C consists of 500 mg TXA dissolved in 250 ml 0.9% NS. In the ivTXA group, Solution A consists of 10 mg/kg TXA dissolved in 100 ml 0.9% NS, Solution B consists of 20 × Wt (mg) TXA dissolved in 100 ml 0.9% NS, and Solution C consists of 250 ml 0.9% NS. In both groups, Solution A will be infused as a bolus intravenously 15 min prior to operation initiation, Solution B will be infused at 5 ml/h intravenously from operation initiation until the last suture (i.e., 1 mg/kg/h TXA infusion in the ivTXA group), and Solution C will be applied for topical wound irrigation for 5 min with the waste fluid removed by suction before the wound is closed.

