### Sample size and statistical analysis

Our pilot cohort study indicated expected TBLs of 971 ± 459 ml and 911 ± 460 ml respectively in the tTXA and ivTXA groups in lumbar spinal decompression and 3–5 levels of bone graft fusion surgeries. Using PASS version 11.0, a sample size of 70 in each group is calculated to be sufficient with assumed type I error rate α = 0.05, power of test 1 – ß = 0.90, and 20% of TBL (195 ml) set as the non-inferiority cut off. Taking into account a dropout rate of 20%, a sample size of 88 in each group is eventually determined.

All the randomized participants who signed the Informed Consent Form (ICF) and satisfied all inclusion/exclusion criteria and have completed demographic data will be included in the intention to treat (ITT) analysis set. All the participants in the ITT set who have completed the perioperative TBL will be included in the per protocol (PP) analysis set. All the randomized participants who have received at least one dose will be included in the safety analysis (SS) set. All the analyses on efficacy will be based on the ITT set. Analysis on AEs will be based on the SS set.

For the primary outcome TBL, statistical methods for continuous variable analysis will be used in the non-inferiority test in the ITT analysis set, and a sensitivity analysis will be conducted in the PP set. The missing data will be treated as missing at random, and the multiple imputation procedure will be used for the primary outcome. The difference between the tTXA group and ivTXA group will be reported as mean difference and lower one-sided 95% confidence interval (CI), along with a one-sided *p* < 0.025.

For other outcomes, the Kolmogorov-Smirnov statistic with a Lilliefors significance level will be used for testing normality for continuous variables. Continuous variables with normal distribution will be compared using the Student *t* test between groups. The continuous parameters with a skewed distribution will be tested with the non-parametric Mann-Whitney *U* test between groups. The categorical variables will be presented as frequencies and percentages and compared using the chi-square test or Fisher’s exact test. If the total number of cases is less than 40 or the minimum expected count is less than 5, Fisher’s exact test will be used.

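### The per protocol set is defined by outcome completion alone, so the planned sensitivity analysis tests missing-data handling and not adherence

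*Protocol article*

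**What the plan says.** All the set definitions stand in the Protocol article, section Sample size and statistical analysis.

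- **ITT.** Randomised participants who consented and "satisfied all inclusion/exclusion criteria and have completed demographic data will be included in the intention to treat (ITT) analysis set".
- **PP.** "All the participants in the ITT set who have completed the perioperative TBL will be included in the per protocol (PP) analysis set".
- **Use of the sets.** "All the analyses on efficacy will be based on the ITT set". For the primary outcome, "a sensitivity analysis will be conducted in the PP set".
- **Missing TBL.** "The missing data will be treated as missing at random, and the multiple imputation procedure will be used for the primary outcome".

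Two other sections bear on the point. Participants adds exclusions for events during the operation: "Participants who undergo dura mater laceration or unexpected massive bleeding or who receive cell saver application during operation will also be excluded". Intervention describes three treatment steps: Solution A as a bolus before the operation, Solution B as an infusion up to the last suture, and the irrigation: "Solution C will be applied for topical wound irrigation for 5 min with the waste fluid removed by suction before the wound is closed". In the tTXA group only Solution C contains TXA. In the ivTXA group only Solutions A and B do.

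**The concern.** In a non-inferiority comparison, a deviation that makes the two arms more alike moves the estimated difference toward zero and so toward the claim. A per protocol analysis is set beside ITT to show whether the conclusion survives when such participants are left out. Here the rule for PP asks only whether the outcome was obtained. Treatment deviators with a TBL value are in both analyses, so the comparison of the two cannot reveal dilution.

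The direction matters for this trial. The pilot means put tTXA 60 ml worse than ivTXA (971 against 911 ml), so dilution would be expected to help tTXA. A reader who sees ITT and PP agree may take that as evidence of robustness to non-adherence, which it would not be.

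This is not detail left to a fuller document. The article states a complete membership rule, and an analysis plan that added adherence criteria would contradict it.

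**Working it through.** **1. Who is in which set**

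| Participant | ITT | PP as defined |
|---|---|---|
| Treated as allocated, TBL obtained | in | in |
| Treated as allocated, TBL missing | in (imputed) | out |
| Major treatment deviation, TBL obtained | in | in |
| Major treatment deviation, TBL missing | in (imputed) | out |
| Eligibility criteria not met | out | out |

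Among participants in ITT, the only thing that decides PP membership is whether TBL is present. The contrast between the two analyses is multiple imputation against complete cases.

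**2. Which deviations favour the claim**

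- *Toward non-inferiority:* solutions swapped between arms; a shortened TXA infusion in the ivTXA arm; systemic TXA given to a tTXA participant.
- *Against non-inferiority:* omitted irrigation in the tTXA arm, because that participant then receives no TXA.
- *No TXA lost:* omitted irrigation in the ivTXA arm, or a shortened infusion in the tTXA arm. Both are saline.

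Only the first group is the concern.

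**3. Inputs**

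- Margin 195 ml and SDs 459 and 460 ml (460 used): Sample size and statistical analysis.
- One-sided 0.025: the p-value criterion stated there for the primary outcome.
- Group sizes: the plan's dropout step reproduces, 70/0.80 = 87.5, rounded up to 88. If every dropout lacks TBL, PP has about 70 per arm. The figure of 70 itself does not reproduce with the pilot difference in its stated direction. That is a separate matter, and 70 and 88 serve here only as group sizes.
- Dilution d: **assumed**, because the documents give no deviation rate. Range shown: 5% to 20%.

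**4. Effect of dilution**

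Let the full-adherence excess of tTXA equal the margin, and let a fraction d of one arm respond like the other arm. Then

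- expected difference: D = 195 × (1 − d)
- standard error: SE = 460 × √(2/n), which is 69.3 ml at n = 88 and 77.8 ml at n = 70
- chance of declaring non-inferiority ≈ Φ((195 − D)/SE − 1.96)

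Example, d = 10%, n = 88: D = 175.5 ml, and Φ(19.5/69.3 − 1.96) = Φ(−1.68) ≈ 4.7%. The noncentral t calculation gives 4.6%. Results by noncentral t:

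| d (assumed) | D (ml) | 88 per arm | 70 per arm |
|---|---|---|---|
| 0 | 195 | 2.5% | 2.5% |
| 5% | 185.25 | 3.4% | 3.3% |
| 10% | 175.5 | 4.6% | 4.4% |
| 20% | 156 | 8.1% | 7.2% |

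The 88 column treats every randomised participant as a full observation. The 70 column is closer to PP as the plan expects it. Both show the inflation, since both sets keep deviators with a TBL value. A set without the deviators would return to 2.5%, but only if their removal were unrelated to blood loss.

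**The case against.** Several points on the other side are sound, and they limit what can be claimed.

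- **Deviations may be rare.** Treatment is one operative session with nurse-prepared solutions checked against the ID number and saline counterparts in each arm, and conduct is audited every 2 months. No section mentions rescue or open-label TXA. The true rate could be well below 10%. This stands, and the rates above are illustrations only.
- **PP is not without any protection.** Eligibility is already required for ITT, and PP is a subset of it. A reader might infer that ineligible participants also remain in PP. The definitions do not support that.
- **The two analyses need not agree.** A reader might infer that they rest on one missing-data assumption and must coincide. They do not. Imputation under missing at random can use other recorded data, while an unadjusted complete-case comparison needs missingness unrelated to TBL within arm. At the planned 20% dropout the sets could differ by about 18 of 88 per arm, and the results could diverge. That divergence would speak to missing data, however, and not to adherence.
- **Type I error depends on the target.** For the effect as randomised, a true difference of 175.5 ml lies inside the margin, and declaring non-inferiority is no error. The inflation refers to the effect under full adherence.
- **A true PP set can itself mislead.** Exclusion for antifibrinolytic use after randomisation may be prompted by bleeding. If such use were commoner under tTXA, it would remove heavy bleeders from that arm and favour the claim.

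None of this supplies an adherence criterion to the PP rule.

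**Conclusion.** The point holds in a limited form. The set called per protocol is a complete-case set, and the sensitivity analysis planned in it examines missing data and not adherence. Participants whose deviations make the arms alike stay in both analyses. The defect is certain from the text; its practical size is not. At assumed dilution of 5% to 20%, the chance of declaring non-inferiority at a full-adherence excess equal to the margin goes from 2.5% to about 3.3–8.1%, depending on the rate and on whether 70 or 88 per arm is taken. This assumes a common SD of 460 ml, one-sided 0.025, and deviations that act only toward zero.

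A reader might infer that the trial's error rate is in fact inflated, or that every treatment deviation favours tTXA. The documents give no rate to support the first, and the omitted-irrigation case contradicts the second. Nor do they commit the trial to success in both sets: PP has the role of a sensitivity analysis, and a requirement to win in both would be a design preference. The change is worth making because it is cheap and the article describes the trial as still recruiting.

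**What to change.** 1. Rename the current PP set complete-case and keep it as the sensitivity analysis for missing data.
2. Define PP as ITT participants with a TBL value who received Solutions A, B and C as allocated, without a major treatment deviation. List the major deviations in advance.
3. Fix PP membership blind to allocation and outcome before database lock. Whether the solutions matched the allocation can be confirmed, as yes or no only, by someone with access to the allocation list who takes no part in the analysis.
4. Report the non-inferiority comparison in PP beside ITT and discuss any discordance.
5. If non-study antifibrinolytic use is a PP exclusion, also report the result with those participants kept, because the use may have been prompted by bleeding.

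The cost is a wording change, one further analysis and a blinded deviation review, which the existing two-monthly audit of conduct and source documents can support. The new PP set will be smaller than the complete-case set and possibly selective, so it should be read beside ITT and not in place of it.

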### Randomization and concealment

Prior to study initiation, an independent researcher who has no contact with any participant will use SAS 9.4 software (SPSS Inc., Chicago, IL, USA) to generate a blocked random number table (block size = 4) to divide eligible participants in a 1:1 ratio into either the tTXA or ivTXA group. Both the participants’ ID numbers and their respective treatment groups (tTXA or ivTXA) will then be sealed in an envelope and made available only to an appointed nurse who is uninvolved in the study conduction.

Participants and researchers will all be blinded to the group allocation. However, at any time point during or after surgeries, any clinician can be “unblinded” to a patient’s treatment group in case of an apparent or suspected medical emergency. A copy of the consent form will be placed inside every chart, and there will also be a note on the front cover of the chart informing that the patient is enrolled in the study, along with contact numbers of the researchers.

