### Outcomes

#### Primary outcome

The primary outcome of this study will be the perioperative total blood loss (TBL), which is the accumulation of the gross blood losses since operation initiation until postoperative day 3 (POD3). TBL is calculated using the formula provided by Gross [16]:$$ \mathrm{Total}\ \mathrm{blood}\ \mathrm{loss}=\mathrm{PBV}\times \left({\mathrm{Hct}}_{\mathrm{pre}}-{\mathrm{Hct}}_{\mathrm{post}}\right)/{\mathrm{Hct}}_{\mathrm{ave}} $$where PBV refers to the patient’s blood volume, Hct_pre_ is the initial preoperative hematocrit, Hct_post_ is the hematocrit on POD3, and Hct_ave_ is the average of the Hct_pre_ and the Hct_post_.

PBV is then calculated using the formula proposed by Nadler et al. [17]:$$ \mathrm{PBV}={\mathrm{k}}_1\times \mathrm{height}{\left(\mathrm{m}\right)}^3+{\mathrm{k}}_2\times \mathrm{weight}\ \left(\mathrm{kg}\right)+{\mathrm{k}}_3 $$where k_1_ = 0.3669, k_2_ = 0.03219, and k_3_ = 0.6041 for men, and k_1_ = 0.3561, k_2_ = 0.03308, and k_3_ = 0.1833 for women.

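### No baseline adjustment is specified for the primary TBL comparison, although TBL is calculated from baseline values that every analysed participant has; adjusting would gain precision at no cost

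*Protocol article*

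**What the plan says.** All references are to the protocol article.

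- **Sample size and statistical analysis.** The primary method is given as "statistical methods for continuous variable analysis will be used in the non-inferiority test in the ITT analysis set". Missing TBL is multiply imputed, and the result is a mean difference between tTXA and ivTXA with a one-sided limit. No model or covariate is named. The Student and Mann-Whitney tests are assigned to the other outcomes, not to TBL.
- **Primary outcome.** TBL is blood volume times the fall in hematocrit, divided by the average hematocrit. Blood volume comes from height and weight with sex-specific constants. One hematocrit term "is the initial preoperative hematocrit". Under Secondary outcomes, any transfused volume is added.
- **Participants.** Eligible patients are those "requiring lumbar spinal decompression and 3–5 levels of bone graft fusion surgeries".
- **Randomization and concealment.** A list in blocks of 4 is used "to divide eligible participants in a 1:1 ratio into either the tTXA or ivTXA group". No stratification factor is mentioned.
- **Planning values.** "expected TBLs of 971 ± 459 ml and 911 ± 460 ml respectively in the tTXA and ivTXA groups", with "20% of TBL (195 ml) set as the non-inferiority cut off".

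**The concern.** Blood volume multiplies the hematocrit part of TBL, so some of the spread between patients is body size by construction. The number of levels fused probably matters too: the Discussion says that blood loss rises with surgical complexity, and the eligible range is three to five levels. Blocking without stratification balances the arm totals, but leaves sex, size and levels to chance.

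If the analysis is a simple difference in means, this predictable variance stays in the interval that decides non-inferiority. The trial has little precision to spare, because under its own planning values its power is well below the stated 0.90. If the model is instead left open until the data are seen, a choice between an adjusted and an unadjusted result remains available when it should already be closed.

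**Working it through.** **Inputs from the document.** Expected TBL 971 (SD 459) ml for tTXA and 911 (SD 460) ml for ivTXA. The expected difference is 971 − 911 = +60 ml against tTXA. Pooled SD = √((459² + 460²)/2) = 459.5 ml. Margin 195 ml. Evaluable size 70 per arm, and 70/0.8 = 87.5, so 88 randomised. The analysis criterion is "along with a one-sided *p* < 0.025"; the sample size uses "assumed type I error rate α = 0.05", with no side stated.

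**The plan's own figure.** n per arm = 2 × [459.5 × (1.960 + 1.282)/(195 − d)]² at one-sided 0.025 and power 0.90.

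- d = +60 (distance 135 ml): 244 per arm. At one-sided 0.05 it is 199.
- d = 0 (distance 195 ml): 117 per arm, or 96 at one-sided 0.05.
- d = −60 (distance 255 ml): 69 per arm by the normal formula and 70 by the t distribution.

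The stated 70 is therefore not reproduced with the stated direction of difference. It appears only if the 60 ml disadvantage is entered as an advantage. That is a separate point; it matters here only as the baseline for the gain.

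**Effect of adjustment.** Residual SD = 459.5 × √(1 − R²). Standard error = residual SD × √(2/n). Power comes from the noncentral t with 2n − 2 degrees of freedom and noncentrality (195 − d)/SE. The few degrees of freedom used by the covariates are ignored.

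**R² is an assumption.** The documents give no correlation, no spread of blood volume and no effect per level. Simulating blood volume from the article's formula, with assumed heights and weights (coefficient of variation of blood volume 16%), gives about 0.10 for blood volume alone. Adding an assumed 100–200 ml per extra level gives about 0.14–0.22. The working range is therefore 0.10–0.22, and its upper part depends on levels being available.

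One-sided 0.025:

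| n per arm | R² | residual SD (ml) | SE (ml) | 95% half-width (ml) | power, +60 ml | power, 0 ml |
|---|---|---|---|---|---|---|
| 70 | 0 | 459.5 | 77.7 | 154 | 0.41 | 0.70 |
| 70 | 0.10 | 435.9 | 73.7 | 146 | 0.44 | 0.75 |
| 70 | 0.22 | 405.8 | 68.6 | 136 | 0.50 | 0.81 |
| 88 | 0 | 459.5 | 69.3 | 137 | 0.49 | 0.80 |
| 88 | 0.10 | 435.9 | 65.7 | 130 | 0.53 | 0.84 |
| 88 | 0.22 | 405.8 | 61.2 | 121 | 0.59 | 0.89 |

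Example, first row: SE = 459.5 × √(2/70) = 77.7, and noncentrality = 135/77.7 = 1.74, which gives 0.41.

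In equivalent sample size, 70 per arm becomes 70/(1 − R²) = 78 to 90, and 88 becomes 98 to 113.

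**Limit of the gain.** With a true excess of 60 ml at one-sided 0.025, adjustment alone reaches 90% power only if R² is about 0.72 (70 per arm) or 0.64 (88 per arm), far above the working range.

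**The case against.** A reader might infer that the protocol has chosen an unadjusted primary analysis. The text does not say so. A covariate-adjusted linear model also yields a mean difference with a confidence limit, and the named two-sample tests are reserved for other outcomes. What is shown is that no adjustment is specified. A full protocol or analysis plan, not shown, could name covariates, and articles often leave that detail out.

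A reader might also infer that the unadjusted result would be biased or invalid. It would not: with 1:1 randomisation the difference in means is unbiased, and its interval already allows for chance imbalance. The loss is precision only.

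Nor do the documents show that all the useful covariates are already collected. Sex, height, weight and preoperative hematocrit must be, because TBL cannot be computed without them. Fused levels appear only as an eligibility range. Levels actually fused are settled during surgery, after randomisation and after the first study infusion, so they are not a clean baseline covariate.

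Finally, the size of the gain rests on an assumed R². Larger values give more impressive figures, but the illustration supports only about 0.10–0.22.

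These objections narrow the claim but do not remove it. The wording fixes no model for an outcome built from known baseline quantities, and a named adjusted model is a better method available without new data.

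**Conclusion.** The point stands as a worthwhile improvement in precision, not as an error that invalidates the comparison. Under the article's SD, margin and expected 60 ml excess, at one-sided 0.025 and an assumed R² of 0.10–0.22, power gains about 4 to 9 points at 70 per arm and 4 to 10 points at 88. The 95% half-width shrinks by about 5% to 12% at either size, since √0.90 = 0.949 and √0.78 = 0.883.

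It would be wrong to infer that adjustment rescues the trial's power. At the planned 70 evaluable per arm it remains at or below about 0.50 with the expected excess. The shortfall from 90% lies in the sample size calculation and needs its own correction.

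**What to change.** Before unblinding, state the primary model:

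- Fit a linear model of TBL on arm, sex, estimated blood volume and preoperative hematocrit. Add the number of fused levels planned before surgery if that is recorded; do not use the number actually fused.
- Put the same variables in the imputation model, fit the analysis model in each imputed data set, and combine the results.
- Compare the upper confidence limit of the adjusted tTXA minus ivTXA difference with 195 ml, since more blood loss is worse.
- Keep the unadjusted difference as a sensitivity analysis.

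If an unshown analysis plan already names such a model, it is enough to confirm that it matches this and was fixed before unblinding. The cost is a few sentences in the analysis plan. No new patients are needed, and no new data beyond what TBL already requires.

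### The only sensitivity analysis named for missing TBL is a complete-case analysis, so its agreement with the imputed result is no evidence that data are missing at random

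*Protocol article*

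**What the plan says.** All statements are in the Protocol article, section Sample size and statistical analysis.

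- Primary analysis, in the ITT set: "The missing data will be treated as missing at random, and the multiple imputation procedure will be used for the primary outcome".
- Sensitivity analysis: "a sensitivity analysis will be conducted in the PP set". No other is named.
- Definition of that set: "All the participants in the ITT set who have completed the perioperative TBL will be included in the per protocol (PP) analysis set". It has no adherence criterion; what separates it from the ITT set is an observed TBL.
- Expected loss: "Taking into account a dropout rate of 20%, a sample size of 88 in each group is eventually determined".
- Test level: a non-inferiority cut-off of 195 ml, reported "along with a one-sided *p* < 0.025".

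Under Primary outcome, TBL is computed from the hematocrit on postoperative day 3 (POD3). A participant without that value has no TBL.

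**The concern.** A sensitivity analysis for missing data should show what happens when the primary assumption fails. This one cannot. The completers' mean difference is unbiased if missingness is unrelated to TBL within each arm, or if the resulting errors cancel between arms. Imputation under MAR needs missingness to be unrelated to TBL only after conditioning on arm and whatever else the imputation model holds. The check therefore needs as much as the analysis it is meant to check, or more.

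At stake is the direction of error. If heavy bleeders are more likely to lack a POD3 hematocrit, and the tTXA arm truly bleeds more, tTXA loses more of its high values. The observed difference shrinks towards zero, which favours the non-inferiority claim. Both planned analyses can then give the same biased answer, and their agreement would be reported as robustness.

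**Working it through.** **The plan's own figure.** 70 / (1 − 0.20) = 87.5, rounded up to 88 per arm. The dropout step reproduces. Whether 70 itself follows from the stated power inputs is a separate question and does not enter here.

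**Inputs from the article.** 88 per arm, with allocation "to divide eligible participants in a 1:1 ratio into either the tTXA or ivTXA group"; SD about 460 ml ("Our pilot cohort study indicated expected TBLs of 971 ± 459 ml and 911 ± 460 ml respectively in the tTXA and ivTXA groups"); margin 195 ml; one-sided 0.025. The test is taken as the upper confidence limit of tTXA minus ivTXA falling below 195 ml.

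**Assumptions, not in the article.** Normal TBL; true difference exactly 195 ml; logit of the probability of missing TBL = a + b × TBL/460, the same in both arms, with a set to give the stated missing rate overall.

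**Formulae.** Bias = 195 − expected completers' difference. SE = √(SD₁²/n₁ + SD₂²/n₂) among completers. False non-inferiority ≈ Φ(−1.96 + bias/SE).

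20% missing overall:

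| Slope b | Missing tTXA / ivTXA | Completers' difference (ml) | Bias (ml) | SE (ml) | False non-inferiority |
|---|---|---|---|---|---|
| 0 | 20.0 / 20.0% | 195.0 | 0 | 77.5 | 2.5% |
| 0.5 | 21.6 / 18.4% | 188.0 | 7.0 | 76.1 | 3.1% |
| 1 | 22.9 / 17.1% | 173.4 | 21.6 | 73.1 | 4.8% |
| 2 | 24.4 / 15.6% | 148.5 | 46.5 | 67.7 | 10.1% |

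Example, b = 1: the completers' SDs are 431.2 and 436.1 on 88 × 0.771 = 67.8 and 88 × 0.829 = 73.0 participants, so SE = 73.1. Then Φ(−1.96 + 21.6/73.1) = Φ(−1.66) = 0.048.

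**Simulation with imputation by arm and no covariates.** At b = 0.5 / 1 / 2, false non-inferiority is 3.1 / 4.9 / 8.9% for imputation and 3.0 / 4.9 / 10.0% for completers. The two estimates differ by about 6 ml per trial on average.

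**Less missing data.** Completers simulated at b = 0.5 / 1 / 2 give 2.9 / 4.0 / 6.7% at 10% missing and 2.8 / 3.1 / 4.5% at 5% missing.

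**Outcome-related dropout in the tTXA arm only** (ivTXA dropout random, 20% missing). Completers give 7.5 / 18.0 / 36.6% and imputation by arm gives 7.9 / 18.2 / 35.7%, with the same bias in both (−44 / −79 / −119 ml). In simpler terms, bias = 0.20 × the excess TBL of tTXA dropouts over tTXA completers. An excess of 200 ml gives 40 ml; with SE = 460 × √(2/70) = 77.8 ml, Φ(−1.96 + 40/77.8) = 7.4%.

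**Identical selection relative to each arm's own mean** (slope 1 in both). No bias; simulated false non-inferiority 2.6%.

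**An early blood-loss covariate in the imputation model** (assumed correlation with TBL 0.5 to 0.7, slope 1, tTXA arm only). If dropout is driven by that covariate, imputation corrects it (2.4%) while completers do not (8 to 11%). If dropout is driven by TBL itself, imputation still gives 8.4 to 12.7%, against 17.6% for completers.

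**The case against.** MAR imputation is a standard primary choice. The imputation covariates, and any delta or tipping-point analysis, are details that an article commonly leaves to an analysis plan, and that plan is not shown. This stands against any claim that such an analysis is missing. It does not answer the point made here: the article itself names the check and defines the set, and no added detail turns a complete-case analysis into a test of MAR.

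A reader might infer four stronger things that the article does not support.

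- *The two analyses must agree.* That holds only if the imputation model contains nothing but arm. The article does not state the model, and with early blood-loss covariates the two can differ.
- *Dropout is shown to be related to bleeding.* The adverse-event section provides for breaking the blind and treating the patient, and the safety outcomes list discontinuation due to adverse events. Neither says that the POD3 hematocrit is then lost, and both interventions are over by wound closure. A link between bleeding and missing TBL is possible but not documented.
- *20% of TBL values will be missing.* This is a planning allowance. TBL is fixed by POD3, so actual loss may be smaller.
- *The intraoperative exclusions for massive bleeding or cell saver use prove the case.* The ITT set requires all eligibility criteria to be met, so as written these participants are in neither analysis and are never imputed. That is a separate problem, which a delta analysis would not reach.

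**Conclusion.** The point holds in this limited form: the named sensitivity analysis cannot support the MAR assumption behind the primary result. Both analyses can be biased towards non-inferiority, but only if dropout depends on TBL beyond the imputation model and does so on the absolute scale or more strongly under tTXA. With a shared mechanism the effect runs from negligible (about 3%) to a fourfold inflation (about 10%) at 20% missing, and is small at 5% missing. It is larger if only tTXA dropout depends on outcome. Slopes, mechanism and missing rates are all assumed, so this shows that the plan is exposed, not that the trial's result will be wrong. It is a cheap improvement worth making, not a fatal defect.

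**What to change.** 1. Keep MAR multiple imputation as the primary analysis.
2. Include in the imputation model what is already collected before POD3: intraoperative loss, drainage at 24 and 48 h, hemoglobin nadir and transfused volume. For drainage, use raw volume and drainage hematocrit. The calculated postoperative loss divides by the average hematocrit, which as defined for TBL needs the POD3 value that is missing.
3. Pre-specify, before unblinding, a delta-adjusted tipping-point analysis. Add increasing amounts to the imputed tTXA values over a range that includes +195 ml, and report the delta at which non-inferiority is lost.
4. Keep the completers analysis if wanted, but do not present it as a test of MAR.

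No single delta should be a pass/fail rule. An addition of 195 ml equals the non-inferiority null only if the arms' imputed means are equal; on the pilot means it would place tTXA dropouts (971 − 911) + 195 = 255 ml above ivTXA.

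Cost: a few extra analysis runs, with no new patients or data. The robustness statement may be less favourable: at 20% missing, +195 ml moves the estimate by 0.20 × 195 = 39 ml, about half of the 77.8 ml standard error.
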